# The effect of pain management group on chronic pain and pain related co-morbidities and symptoms. A stepped-wedge cluster randomized controlled trial. A study protocol

**DOI:** 10.1016/j.conctc.2020.100577

**Published:** 2020-06-18

**Keywords:** Pain management, Chronic pain, Self-efficacy, Health services, Occupational health

## Abstract

**Introduction:**

In primary care settings, pain-management group therapy is a tool potentially cost-effective but very much underused.

**Methods:**

Our purpose here is to provide useful scientific information on the effect of pain-management group participation on chronic pain and pain-related co-morbidities and symptoms, as well as practical information for primary and occupational health services to initiate pain-management group activity.

This study will be carried out at primary care Occupational Health Helsinki (Helsinki city employees' occupational health services), with the Finnish Institute of Occupational Health as the research partner.

This is a stepped-wedge cluster randomized controlled trial among both male and female municipal employees aged 18 to 65, all of whom had visited an occupational doctor, nurse, psychologist, or physiotherapist because of any chronic pain unrelated to malignant disease. An additional inclusion criterion is work disability risk being elevated, based on a short screening questionnaire (modified Örebro questionnaire). Each participant and each interviewer will be blinded at randomization.

Three groups, 10 subjects in each, begin directly after recruitment with 6 weekly 2-h meetings and a follow-up meeting 6 months later. Three waiting-list groups begin 4 months later. Subjects complete self-administered questionnaires before and after the sixth meetings, also 6 months later. Primary outcomes are pain intensity, current work ability, pain self-efficacy, fear-avoidance beliefs, chronic pain acceptance, depressive symptoms, sleep problems, sickness absence days, and number of occupational health care contacts from OH's medical records.

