### Sample size calculation

2.2

In this study we have 9 outcomes. In the presence of several outcomes, sample size should be calculated for the outcome with the smallest difference in effect size before and after [40]. Chronic pain patients' pain is usually high, even 7 or higher, and pain often remain with no change in clinical treatment studies. Minimal cut-off change for pain has been detected in previous studies. Salaffi et al., 2004 [41] stated that minimal cut-off point measure of Numeric Rating Scale of NRS pain is −1.0 cm. When pain is 7.5 before intervention, and after intervention 6.5, the effect size is 13%. The difference in pain acceptance and fear-avoidance beliefs may even be larger than 15% pre- and post-intervention [41]. By using stepped wedge analysis on the study design matrix (6 groups with 4 observations of each group) and with 15% detectable minimum difference of the outcome (chronic pain, mean 7.14 in a scale from 0 to 10) we calculated the minimum group sample size to be 10 (when a-error is 0.05 and b-error 0.80) and total number of participants to be 60 [42].

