### Data collection

2.7

Data collection can be seen in Table 2. Variables. During the recruitment, a short screening questionnaire (Scr), a slightly modified version of the validated Örebro Short Questionnaire is filled out [45]. A question as to the pain lasting more than 3 months is not calculated, it is one of the inclusion criteria. The sum score is calculated based on 10 questions, each earning 0–10 points: pain areas, (head, neck-trapezius, shoulder/upper arm, elbow or lower arm, wrist/hand, upper back, lower back, hip/thigh, knee/shin, ankle/foot-pain), pain intensity, anxiety, depressive symptoms, being able to do light work for an hour, sleep, expected risk of pain remaining persistent, self-perceived ability to work within the next 3 months, two items on fear-avoidance: “I should stop what I am doing until the pain decreases” and “I should not do normal activities or work when I feel pain”. Maximum sum is 100 points.

**Table 2 tbl2:** Variables.

Variables		Questionnaires			
		Scr	Bef1, Bef2	Aft	Aft 6 m, Aft 12 m
*Outcomes*					
	Pain intensity, 1 item (0 = no pain, 10 = the worst possible pain)	x	x	x	x
	Current work ability, 1 item (0 = totally disabled, 10 = the ability to work at its best)		x	x	x
	Pain self-efficacy, 10 items (0 = not at all confident, 6 = completely confident)		x	x	x
	Chronic pain acceptance, 8 items (0 = totally disagree, 6 = totally agree)		x	x	x
	Depressive symptoms, 1 item (0 = not at all, 10 = extremely much)	x	x	x	x
	Sleep problems, I can sleep at night (0 = I can do it despite pain, 10 = I can't do it because of the pain problem)	x	x	x	x
	Sleep problems, days slept well during the past week (0–7)		x	x	x
	Sickness-absence days (6 months before and after intervention)				
	Health care contacts, number of contacts (6 months before and after intervention)				
*Pain-related variables*	Pain areas, 10 areas (0 = no, 1 = yes)	x	x	x	x
	Pain-related fear-avoidance, 2 items (0 = totally disagree, 10 = totally agree)	x	x	x	x
	Fear of movement, 3 items (0 = totally disagree, 6 = totally agree)		x	x	x
	Self-perceived risk of current pain becoming persistent (0 = no risk, 10 = very large) risk)	x	x	x	x
	Use of painkillers during the previous week, 3 items (0 = none, 1 = few times a week, 2 = every day) Anti-inflammatory drug or Paracetamol Strong analgesic, opiate, medications for chronic pain		x	x	x
	Other medication (open question)		x	x	x
	Non-pharmaceutical pain management tools (open question)		x	x	x

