### Outcomes

2.8

Outcomes, variables, and covariates are listed in Table 2.

Outcomes are pain intensity, current work ability, pain self-efficacy, pain-related fear avoidance beliefs, chronic pain acceptance, depressive symptoms, sleep problems, sickness absence days and number of occupational health care contacts which are collected from OH's medical records.

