### Statistical analysis

2.11

The post-intervention period is compared with the pre-intervention (control) period. Linear mixed-effect models allow analysis of repeated measures data and the differences in the outcomes of interest between intervention and control periods. Intention-to-treat analyses are conducted, and time-effect and intra-cluster correlation coefficients reported. When the null hypothesis (i.e., no difference) is rejected, it is always possible to conclude, whatever the results of the study are, that there exists a difference but actually there is not (type-I error or false positive) [51]. Since the sample size is rather small, exact confidence interval for outcomes will be the choice to avoid statistical bias and false-positive or false-negative errors [51].

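### Nine outcomes are labelled primary and none is ranked, the outcome lists disagree, and exact confidence intervals cannot do what Section 2.11 claims for them

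*Protocol article*

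**What the plan says.** - **Abstract, Methods:** "Primary outcomes are pain intensity, current work ability, pain self-efficacy, fear-avoidance beliefs, chronic pain acceptance, depressive symptoms, sleep problems, sickness absence days", followed by the number of occupational health care contacts. That makes nine.
- **Section 2.2:** "In this study we have 9 outcomes". For several outcomes the rule is that "sample size should be calculated for the outcome with the smallest difference in effect size before and after". The calculation is then done for pain, "when a-error is 0.05 and b-error 0.80" (I read the second figure as power of 0.80). This is the only significance level in the article.
- **Section 2.8:** "Outcomes are pain intensity, current work ability, pain self-efficacy, pain-related fear avoidance beliefs, chronic pain acceptance, depressive symptoms", then sleep problems, sickness absence and health care contacts. These are the same nine, without the word primary and without any order of importance.
- **Table 2 (Section 2.7):** the outcomes block also has nine rows, but not the same nine. Sleep takes two rows, the second being "Sleep problems, days slept well during the past week (0–7". Fear-avoidance is placed further down, among the pain-related variables: "Pain-related fear-avoidance, 2 items (0 = totally disagree, 10 = totally agree".
- **Section 2.10:** a separate before-and-after question is posed for each of the seven questionnaire outcomes.
- **Section 2.11:** linear mixed models compare the post-intervention period with the control period. Because the sample is small, "exact confidence interval for outcomes will be the choice to avoid statistical bias and false-positive or false-negative errors".

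**The concern.** A primary outcome is what a trial is judged on. With nine carrying that label, no ranking and no statement of whether one or all must succeed, a single significant result among nine could be reported as a positive primary finding. The 0.05 used in the sample size would then not be the trial's actual chance of a false-positive primary claim.

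Two statements in the article make this worse. The lists do not agree on which nine outcomes are meant, so it is unclear whether fear-avoidance is inside or outside the set and which sleep item counts. And the sentence that addresses false positives names a tool that does not limit them across outcomes, so a reader may believe the matter is settled.

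**Working it through.** **1. The plan's own figure.** Section 2.2 gives a 15% difference on a mean of 7.14, so the detectable difference is 0.15 × 7.14 = 1.071 points. Six groups of 10 give 60. Neither a standard deviation nor an intra-cluster correlation is stated, so 60 can be neither reproduced nor refuted. What matters here is that it uses one alpha of 0.05 for one outcome. The rule of sizing on the smallest effect concerns power and leaves type I error across outcomes untouched.

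**2. Family-wise error.** Inputs: nine outcomes (abstract, Sections 2.2 and 2.8) and alpha 0.05 (Section 2.2). Assumptions: each outcome is read at 0.05, and any one counts as success.

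- Independent outcomes: 1 − 0.95^9 = 1 − 0.630 = 0.370.
- Upper bound under any dependence: 9 × 0.05 = 0.45.
- Simulated equicorrelated normal test statistics, two-sided (the correlations are assumed; the article gives none):

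| Pairwise correlation | Chance of at least one false positive |
|---|---|
| 0.3 | 0.33 |
| 0.5 | 0.27 |
| 0.7 | 0.20 |
| 0.9 | 0.12 |

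Even at 0.9 the figure is more than twice 0.05.

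**3. The opposite success rule.** If all nine had to succeed, no alpha split would be needed. With 80% power each and independence, however, the chance of success would be 0.8^9 = 0.13. The article states neither rule.

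**4. The lists side by side.**

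| | Abstract and Section 2.8 | Table 2, outcomes block |
|---|---|---|
| Fear-avoidance | included | absent (under pain-related variables) |
| Sleep | one entry | two items |
| The other seven | same | same |
| Count | 9 | 9 |

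The count in Section 2.2 therefore fits two different sets. Section 2.9 does not name fear-avoidance among the pain-related variables, so the running text is consistent and Table 2 is the outlier.

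**5. What an exact interval does.** It secures the stated coverage for one parameter when large-sample approximations are doubtful. Nine exact 95% intervals, if independent, all cover their true values with probability 0.95^9 = 0.63. The 0.37 from step 2 is unchanged. False negatives depend on N, variance and true effect. At fixed N and alpha, making the interval exact does not reduce them.

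**6. Price of keeping all nine primary.** The strictest Holm step, equal to Bonferroni, is 0.05 / 9 = 0.0056. For an outcome with exactly 80% power at two-sided 0.05, the standardised effect is 1.960 + 0.842 = 2.802. The critical value at 0.0056 two-sided is 2.773, so power is Φ(2.802 − 2.773) = 0.51. Restoring 80% needs a factor of ((2.773 + 0.842) / 2.802)² = 1.66, or about 60 × 1.66 ≈ 100 participants if N scales with information. Holm does at least as well as this, because later steps are less strict.

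**The case against.** The strongest reply is that this is a condensed article. A multiplicity method and success rule may sit in an analysis plan that is not shown, and the word primary is attached to these outcomes only in the abstract. The first part is right as far as it goes: absence of an adjustment method is not the finding. But the label on nine outcomes is a choice this article makes, and the body, which ranks none, does not correct it.

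Other parts of the reply stand and limit the point:

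- No sentence says each outcome is tested at 0.05. That is inferred from the single alpha and the separate questions in Section 2.10. The error rates are conditional on it and on an any-one rule.
- The Introduction says that pain, depression and sleep problems occur together, so 0.37 is not the most realistic value.
- The exact-interval sentence is motivated by the small sample and does not mention several outcomes. It should not be read as a failed multiplicity procedure. It is wrong on its own terms, because it promises to avoid errors that exactness does not remove.
- Sections 2.2 and 2.10 themselves say that pain often changes little in treatment studies. The choice of a single primary outcome therefore belongs to the investigators.

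Two stronger readings are tempting but unsupported. A reader might infer testing at three post-intervention times, which would multiply the tests. Section 2.11 reads as one pooled post-versus-pre contrast per outcome, the two register outcomes have a single window of 6 months before and after, and the 12-month questionnaire covers only groups A to C. A reader might also count ten primary outcomes. Ten arises only by merging the text list with the Table 2 list; each list has nine.

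**Conclusion.** The point holds in three parts.

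1. Nine outcomes are labelled primary and none is ranked. If each is read at 0.05 and any one suffices, the family-wise error is 0.37 under independence and about 0.20 to 0.33 at assumed correlations of 0.7 to 0.3. The count and the alpha come from the article; the decision rule and the correlations are assumptions.
2. Table 2 contradicts the abstract and Section 2.8 on fear-avoidance and on the number of sleep items. This needs no assumption.
3. The statement on exact intervals in Section 2.11 is incorrect. This also needs no assumption.

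Nothing here shows that the sample size of 60 is wrong. With one primary outcome it can be kept at alpha 0.05 without change on this account.

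**What to change.** - Designate one primary outcome. Pain intensity is the natural candidate, because the sample size was computed for it. Analyse it with the planned mixed-model post-versus-pre contrast and state which visits enter that contrast. Section 2.2 sized pain over 6 groups with 4 observations each and named no visit, so a particular visit should not be presented as the one that was sized.
- Make the other eight outcomes secondary, either Holm-adjusted or reported as supportive. If the investigators prefer to keep all nine primary, apply Holm across the nine and state the loss of power (from 80% to about 51% at the strictest step).
- Make the abstract, Section 2.8 and Table 2 list the same outcomes, with fear-avoidance placed consistently and one sleep item designated.
- Delete the claim that exact intervals avoid false positives and false negatives. If they are kept, describe them as a small-sample safeguard for the coverage of each interval.

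No extra participants or data are needed with a single primary outcome. The cost is one of substance as well as wording: it changes what the trial is judged on, and the other eight outcomes can no longer each be claimed as a primary result.

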**Results:**

We will publish our results in a peer-reviewed scientific journals.

## Introduction

1

In 2016, low-back pain and migraine were established to be in the top ten of diseases or injuries, causing years lived with disability (YLD) in countries and territories numbering 195 [1]. Among all citizens in European countries and Israel, those reporting moderate or severe chronic pain as lasting at least 6 months, experienced in the previous month, and at least twice a week, has ranged in Europe from 12% to 30%. Pain prevalence by this definition is highest in Norway, Poland, and Italy, and lowest in Spain, Ireland, and the UK [2]. The prevalence of any chronic pain condition, surveyed in 10 developed and 7 developing countries, was higher in women than in men, and the incidence of chronic pain was found to increase with age [5]. In New Zealand, the prevalence of chronic pain is 16.9% [3]. In Finland, the chronic pain prevalence was reported in 2006 to be 19% [2], with approximately one million Finnish chronic pain sufferers, of whom the majority were actively participating in working life [4]. According to the 2006 survey in Europe and Israel Finns were more often absent from work due to chronic pain than are other Europeans, up to three times as often as in Sweden or in the UK [2]. Over 30% of Finns' working days are lost due to pain-related disorders, mainly due to joint pain, neck, arm, and back pain. Furthermore, recurring shoulder and neck pain has burdened more than 40% of working people on Finland [6]. Moreover, the number of disability pensions in Finland due to musculoskeletal disorders has been very high, i.e., about 30% of annually granted disability pensions in 2015 [7].

Chronic pain rarely occurs alone and therefore we chose our outcomes based on the earlier chronic pain research results. Common co-morbidities are depression and sleep problems [[8], [9], [10]]. Those who sleep poorly have reported significantly higher scores on the Beck Depression Inventory (BDI) and higher baseline pain intensity ratings [11]. Moreover, a Chinese study has found obesity to be associated with chronic pain [12]. In a Finnish population-based study among working people, half of the subjects experienced either widespread pain, depression, or sleep disturbance [13], with one-fourth having at least two of these symptoms concurrently. Workers with co-morbid widespread pain, depression, or sleep problems had a 10-fold higher risk for reduced work ability and sickness absences, and their visits to a physician were 4–5 times as high as among those without these symptoms [14]. When pain is associated with inability to work, both women and men are more likely to experience pain in several parts of the body, to smoke, to have a lower level of education, and to be obese [15].

Finland's Current Care Guidelines of chronic pain management recommend primarily non-pharmacological treatment [16,17]. The most useful types of such treatment, based on increasing evidence, include cognitive-behavioral therapy (CBT), exercise, mindfulness-meditation, yoga, acupuncture, and music listening, as well as treatment combining these methods [18].

One cost-effective way to deliver this treatment is via group activity. In several studies, pain management group therapy with a cognitive-behavioral framework had a significant effect on chronic pain [[19], [20], [21], [22]]. CBT often involves learning-attention management, in which attention is moved away from the pain to more meaningful things. Attention management therapy for six weeks has reduced chronic-pain-related anxiety and hyper-arousal as well as reducing the impact of chronic pain on everyday life [23]. CBT alone and in combination with physical therapy has significantly reduced long-term sickness absence and the use of health services among back- and neck-pain patients, when compared to a control group who received only clinical examinations and guidance [19].

Chronic pain patients' pain is usually very high. In neck pain research, mean pain intensity (VAS) of 72 patients was 6.3 cm [24]. Pain experiencing can be affected by fear of the harmful effects of pain, such as pain itself and fear of injury. In addition, patients' pain experience may be widely influenced by factors such as fear, distress and false beliefs of the nature of pain and the outcome of treatment [25]. One meta-analysis concluded that correlation between pain-related fear and disability was 0.50, which makes the connection quite significant [26]. Self-efficacy is protective, whereas fear-avoidance belief is a risk factor for quality of life [27,28]. Health care professionals have been poor at identifying psychological risk factors for low back pain (LBP) like life crises, fear, anxiety and depression [29]. Lethem et al. generated the fear-avoidance model to explain why some individuals having musculoskeletal pain, became chronic, especially lower back pain. The centerpiece of that model is the fear of pain in lifting, bending, or working. Avoidance of such activities exacerbates the fear of pain [30,31].

La Chapelle, Lavoie, and Boudreau showed six different phases in the process of accepting pain [32]. First, the patient feels a need for help, after which the found help usually leads to receiving a diagnosis, then health professionals usually tell the patient a diagnosis, and after that the patient realizes that there is no sudden cure. After all these phases, acceptance leads to understanding that things could be worse, which leads to redefining normal, and after that, acceptance may be seen as an ongoing daily process. Factors that increase pain acceptance can include getting a diagnosis, good social support, educating yourself and others close to you about chronic pain, caring for yourself and being merciful to yourself. Factors preventing pain acceptance can be the struggle to preserve the identity that prevailed before chronic pain, negative relationships, other people not accepting chronic pain, the unspoken messages and spoken messages of other people that a person who looks so healthy cannot be so painful [32]. Pain acceptance has been found to relate to positive mood. Furthermore, when pain acceptance increases the levels of positive feelings, it reduces the negative mood [33].

Physical symptoms often occur without physical illness; this is called “somatization,” when psychological factors cause a symptom. The somatization tendency makes it more likely that one will seek medical help [34]. Somatization may amplify transient pain sensations, making them more persistent [35]. High self-efficacy attenuates the association between perceived pain and somatization and researchers suggest that clinicians should encourage especially those pain patients' self-efficacy, who are predisposed to somatization [36].

The aim of this study is to examine the effectiveness of pain-management group participation on pain intensity and associated disability, pain self-efficacy, fear-avoidance beliefs, acceptance of chronic pain, and co-occurrent mental or sleep problems in patients with chronic pain as well as their perceived ability to work, their sickness absence (SA) due to pain, and their use of health services.

## Methods

2

### Participants and recruitment

2.1

The study base comprises the employees of the city of Helsinki, the country's largest employer. The city of Helsinki has its own occupational health services (OHS), which provides OH services for more than 40 000 employees in 800 occupations of 30 industrial fields. The average age of employees in the city of Helsinki in 2014 was 46, the largest age-group in the city being 50–59. The youngest employees were 19 years old and the oldest employees of the city of Helsinki were 65 [37]. We therefore decide to include employees aged 18–65 years. Systematic review stated that most often the exclusion criteria's were psychological conditions, malignancy, recent or scheduled surgery, pregnancy and trauma [38]. Consistently we will exclude severe diseases such as malignancies, which would lead possibly to missed meetings and lost follow-up, and also we exclude a disease such as severe mental illness, which could bias results [39].

Inclusion criteria•18- to 65-year-old Helsinki city employee•Chronic pain (lasting) for 3 months or longer•Suitable for group activity, by being willing to share own thoughts with other group members•Work disability risk being elevated, based on a short screening questionnaire (modified Örebro questionnaire). Screening survey points for work disability ≥50/100

Exclusion criteria•Malignant disease such as cancer or severe mental disease•Participating in another pain-management group•Experiencing a major psychological or physical life crisis•Being at no elevated risk for work disability, Screening survey (modified Örebro questionnaire) points <50/100

